## Abstract

**Background:**

The COVID-19 pandemic has had drastic consequences on everyday life in nursing homes. Limited personnel resources and modified hygiene and safety measures (eg, no external exercise instructors, no group settings) have often led to interrupted physical exercise treatments. As a consequence, people with dementia benefiting from individualized exercise programs are affected by the pandemic’s impact.

**Objective:**

Our goal is to develop an easily applicable mobile application (Individualized Cognitive and Physical Exercise [InCoPE] app) allowing nursing assistants to test cognitive function and physical performance and subsequently train people with dementia through a multidomain, individualized exercise program.

**Methods:**

We will evaluate the usability and effectiveness of the InCoPE-App by applying a mixed method design. Nursing assistants will use the InCoPE-App for 18 weeks to assess the cognitive function and physical performance of 44 people with dementia every 3 weeks and apply the individualized exercise program. We will record overall usability using questionnaires (eg, Post-Study System Usability and ISONORM 9241/10), log events, and interviews. Perceived hedonic and pragmatic quality will be assessed using the AttrakDiff questionnaire. Effectiveness will be evaluated by considering changes in quality of life as well as cognitive function and physical performance between before and after the program.

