### Intervention

The individualized exercise program for people with dementia is based on earlier work by this research group and includes a combination of cognitive and physical exercises [19]. The included exercises were further differentiated to ensure a higher degree of individualization following the idea of individualized medicine [20]. The individualized exercise program is embedded in the InCoPE-App, which will be utilized by nursing assistants. The InCoPE-App will be installed on a tablet device (Android), and nursing assistants will be trained in the appropriate use of the app in order to test and instruct people with dementia. The training comprises theoretical online modules for self-study (eg, theoretical basics of physical exercise with people with dementia, objective testing of physical and cognitive performance in people with dementia, first steps with the InCoPE-App) and 2 face-to-face meetings (between project members or research staff and nursing assistants) for the usage of the InCoPE-App. The InCoPE-App contains detailed photographic materials and descriptions to offer visual support in the execution of the proposed tests and exercises.

The tests assessing motor and cognitive performance included in the InCoPE-App are based on published recommendations and were used with people with dementia before [21,22]. On the basis of cluster analysis in a large sample of people with dementia who participated in our group’s previous randomized controlled trial [19], we identified 4 homogeneous subgroups of people with dementia [23] who were also considered when we designed the InCoPE-App: participants with (1) below-average motor and cognitive performance, (2) average cognitive performance and above-average motor performance, (3) above-average cognitive and motor performance, and (4) above-average cognitive performance and below-average motor performance. The initial testing of physical and cognitive performance included in the InCoPE-App will be used to determine whether an individual belongs to cluster 1, 2, 3, or 4. Testing will be repeated every 3 weeks during the 18-week intervention period to allow the InCoPE-App to regularly adjust the duration, intensity, and contents of the cognitive and physical exercises based on the individual’s needs. We anticipate that the desired physical and cognitive adaptation to the exercise program will be achieved by gradually increasing exercise difficulty and intensity (eg, number of repetitions).

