### Outcomes

#### Primary Outcomes

The primary outcomes were defined along the overall aim to evaluate the usability and effectiveness of the individualized exercise program delivered via the InCoPE-App. In Table 1, the questionnaires and measures for usability, quality of life, and overall cognition as well as methods to evaluate executive function and physical performance are listed.

**Table 1 table1:** Primary outcomes.

Dimensions	Assessments	Pre	Post	Implemented in the InCoPE^a^-App
Overall usability	Post-Study System Usability Questionnaire (PSSUQ) version 3 [24]	No	Yes	No
Overall usability	ISONORM, a questionnaire that operationalizes the 7 criteria of EN ISO 9241-10 [25]	No	Yes	No
Perceived hedonic and pragmatic quality	AttrakDiff 2 [26]	No	Yes	No
Quality of life	German Quality of Life-Alzheimer’s Disease (QOL-AD) [27]	Yes	Yes	No
Global cognition	Mini-Mental State Examination Test (MMSE) [28]	Yes	Yes	Yes
Executive function	Digit span [29]	Yes	Yes	Yes
Mobility	Timed Up & Go (TUG) test [30]	Yes	Yes	Yes
Mobility	6-meter walking test (6MWT) [31]	Yes	Yes	Yes
Function and strength of lower limbs	Modified 30-second chair stand test (CST) [32]	Yes	Yes	Yes
Balance	Frailty and Injuries: Cooperative Studies of Intervention Techniques-subtest 4 (FICSIT-4) [33]	Yes	Yes	Yes

^a^InCoPE: Individualized Cognitive and Physical Exercise.

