Examination of the effects of the InCoPE-App on physical and cognitive performance in people with dementia will be determined based on the listed variables in Table 1. The primary outcomes will be assessed before and after the 18-week intervention. To assess quality of life, the 13-item caregiver-administered version of Quality of Life-Alzheimer’s Disease (QOL-AD) [27] will be applied. The QOL-AD is a valid and reliable tool (internal reliability, α=0.88-0.89; test-retest reliability for caregivers, 0.92) [27]. Global cognition will be assessed with the MMSE [28]. The questionnaire will be implemented in the InCoPE-App. The MMSE easily assesses 7 areas of cognitive function, with sufficient test-retest reliability (0.80-0.95) [28,36]. To assess executive function, the Digit Span Test [29] will be administered. The Digit Span Test consists of 2 parts: forward and backward. Participants will be asked to repeat a sequence of 3 to 9 digits forward and of 2 to 8 digits backward. The InCoPE-App will be used to document the given answers. The Digit Span is a reliable and valid test [37].

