### Statistical Methods

All analyses will be performed using SPSS 27.0 (IBM Corp, Armonk, NY). Prior to analysis, plausibility (eg, considering range and distribution) will be checked to minimize errors. The quantitative analysis comprises the evaluation of the usability questionnaires, which will be analyzed with respect to the corresponding guidelines and will be compared with representative data.

The baseline values of physical and cognitive performance will be compared between IG and CG using chi-square tests for categorical data, Mann-Whitney *U* tests for nonparametric variables, and t tests for continuous and normally distributed parameters. Normal distribution will be checked with the Shapiro-Wilk test. Means and standard deviations will be calculated for normally distributed data, and medians and interpercentile ranges will be calculated for non-normally distributed data. A 2-factor ANOVA with repeated measurement will be used to identify treatment effects. In addition, 95% confidence intervals and partial Eta² will be calculated. The log events will be summarized and analyzed descriptively. Potential effects among subgroups based on varying physical or cognitive performance, gender, fear of falling, and logged events (completed training sessions, average duration of the training sessions) will be investigated using chi-square tests and *t* tests.

Qualitative content analysis of the field notes will be conducted [48]. The interviews will be fully transcribed and checked for accuracy. The entire coding process will be independently performed by 2 scientists. The transcripts will be reviewed to identify meaningful content-related aspects. These aspects will be systematically described using a category system. Research questions and interview guidelines will be consulted to deductively derive the main categories. Subcategories will be inductively developed based on the findings (eg, by subsumption). The category system will be tested by 2 scientists who will independently test-code several parts of the qualitative material and subsequently adapt the categories and their definitions. The 2 coding systems will eventually be merged by consensual coding where consensus will be reached.

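### The pre/post ANOVA cannot use a resident without a week-18 value, even where 3-weekly readings exist; whether controls have such readings must first be settled

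*Protocol article*

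**What the plan says.** - **Testing schedule.** The Abstract (Methods) has the assistants "assess the cognitive function and physical performance of 44 people with dementia every 3 weeks". The Intervention section says "Testing will be repeated every 3 weeks during the 18-week intervention period" and gives the purpose: letting the app adjust each resident's exercises.
- **Outcomes.** Table 1 lists seven resident outcomes. Six are marked as implemented in the app: MMSE, digit span, Timed Up & Go, 6-meter walk, chair stand and FICSIT-4. QOL-AD is not.
- **Time points.** Primary Outcomes: "The primary outcomes will be assessed before and after the 18-week intervention". The Abstract defines effectiveness by "changes in quality of life as well as cognitive function and physical performance between before and after the program".
- **Analysis.** Statistical Methods: "A 2-factor ANOVA with repeated measurement will be used to identify treatment effects".
- **Controls.** Randomization and Concealment gives the 22 controls conventional treatment only. It does not say whether they are tested in between.

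**The concern.** A repeated-measures ANOVA with two time points needs both values from each resident. Someone tested at week 15 who then dies, moves or is admitted to hospital adds nothing to the effectiveness estimate, although readings from weeks 3, 6, 9, 12 and 15 may be stored in the app.

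Two things are at stake. One is precision, since the 44 residents include no allowance for loss. The other is bias. The Introduction describes rapid progression in many people with dementia, so those who leave may be those who decline. If controls decline more, the missing decliners would make the programme look less effective than it is.

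**Working it through.** **1. Who has interim readings?**
- Abstract: all 44 residents are tested every 3 weeks, but the same sentence also applies the exercise programme to them, and 22 of the 44 are controls (Sample Size).
- Intervention: the testing serves to adjust the exercise, which only the intervention group (IG) receives.
- Randomization and Concealment: limits the control group's (CG) treatment and is silent on its testing.

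The readings are clear for the IG and unsettled for the CG.

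**2. The plan's own figure.** Inputs from Sample Size: partial eta squared 0.07, alpha 0.05, power 0.95. Assumed, because not stated: m = 2 measurements, correlation 0.5.
- f² = 0.07/0.93 = 0.0753, so f = 0.274.
- λ = N·f²·m/(1−ρ) = 44 × 0.0753 × 2/0.5 = 13.25, with 1 and 42 df. Power is 94.5%; the smallest even N for 95% is 46.
- Normal approximation: standardised difference in change 4f = 1.097; 2 × (1.960 + 1.645)²/1.097² = 21.6, so 22 per arm, 44 in all.

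The stated 44 therefore fits a two-time-point analysis with no allowance for loss.

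**3. Power if only residents with both values count.** The loss rates are assumed; the article gives none.

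| Loss | Residents left | Power |
|---|---|---|
| 10% | 40 | 92.2% |
| 20% | 35 | 88.3% |
| 30% | 31 | 84.0% |

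**4. Precision at 20% loss, baseline to week-18 correlation 0.5.** Known covariance, losses spread evenly over visits, separate baseline means per arm.
- Planned ANOVA: 44 × 0.8 = 35.2 effective residents.
- Mixed model on pre/post only. Variance per arm (1−ρ²)/17.6 + (1−ρ)²/22 = 0.75/17.6 + 0.25/22 = 0.0540, against 1/17.6 = 0.0568 for the ANOVA: 5% less variance, 37.1 effective residents.
- Mixed model on all visits, both arms: 38.0 (equal correlations) to 39.2 (correlations that decay with time). 1 − 35.2/38.0 = 7.4%; 1 − 35.2/39.2 = 10.2%.

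Of this, the interim readings themselves add 38.0 − 37.1 = 0.9 to 39.2 − 37.1 = 2.1 residents.

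**5. Precision under a random intercept and slope.** Assumed: intercept SD 0.9, slope SD 0.5 over 18 weeks, error SD 0.4, true effect 0.50, 22 per arm, 20% lost at random. The change score has variance 0.5² + 2 × 0.4² = 0.57, so the ANOVA standard error should be near √(2 × 0.57/17.6) = 0.254.
- Simulated standard errors: 0.259 (planned ANOVA), 0.252 (pre/post, baseline-adjusted), 0.243 (all visits). A separately coded run gave 0.256, 0.250 and 0.242.
- All visits against ANOVA: 1 − (0.243/0.259)² = 12%. Baseline adjustment alone gives 1 − (0.252/0.259)² = 5% of that.
- With the covariance estimated rather than known, and unstructured, the gain fell from 11% to 8%. The uncorrected model standard error averaged 0.235 against an actual 0.253, about 7% too small.
- Pre/post only, separate baseline means: the slope of week 18 on baseline is 0.81/0.97 = 0.835 and the residual variance 1.22 − 0.81²/0.97 = 0.544. Variance per arm is 0.544/17.6 + 0.165² × 0.97/22 = 0.0321, against 0.57/17.6 = 0.0324: about 1% less.

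**6. Bias when decliners leave more often.** Same model, mean estimates, true value 0.50.

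| Run | Lost | Planned ANOVA | Pre/post, baseline-adjusted | All visits, both arms |
|---|---|---|---|---|
| First | 19% | 0.479 | 0.481 | 0.509 |
| First | 26% | 0.430 | 0.436 | 0.497 |
| Second | 19% | 0.47 | 0.47 | 0.50 |
| Second | 31% | 0.41 | 0.41 | 0.48 |

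With interim readings from the IG only, the estimate was 0.425 in the first run and 0.41 and 0.27 in the second, no better than the ANOVA. None of these calculations includes clustering by nursing home.

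**The case against.** The strongest reply is that the plan is coherent as it stands: a before-after contrast, two outcome times, a sample size that fits them, and an aim limited to trends toward effectiveness. On this view the 3-weekly tests are part of the intervention, and the Abstract sentence is loose, since it also gives the programme to controls. If so, no usable two-arm interim data exist, and obtaining them would mean five more test rounds in 22 controls, a design change. This stands as a limit on the point. It does not remove it, because the controls' testing schedule is left open and the ANOVA still discards residents with a baseline only.

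Three stronger readings are tempting and not supported:
- **That all 44 residents have up to five unused readings.** Only the Abstract says so, and in a sentence that cannot be literal for controls in its other half.
- **That the protocol prescribes a completers-only analysis.** It states no rule for missing values, and an analysis plan that is not shown may set one. The point is confined to what the named ANOVA can use.
- **That the quoted reliabilities make interim readings nearly as good as the week-18 value.** Test-retest reliability is not the correlation across weeks in a progressive disease.

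It is also fair that the size rests on assumed loss and correlations, that a known covariance flatters the mixed model, that an unstructured 7-visit covariance (28 parameters) is too much for 44 residents, and that any replacement must reflect the cluster randomisation. FICSIT-4, scored 0 to 5, suits a linear model only roughly, but the same is true of the planned ANOVA.

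**Conclusion.** The point holds in a conditional and modest form. The named analysis cannot use a resident without a week-18 value, even where the app holds interim readings, and the protocol does not settle whether controls have them.

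If both arms are tested every 3 weeks, a mixed model on all visits would give roughly 7-12% less variance than the planned ANOVA at an assumed 20% loss. The upper end includes about 5 points from baseline adjustment and treats the covariance as known. It would also remove most of the attrition bias in the scenarios tried. There the ANOVA understated the effect by 0.02 to 0.09, at most 0.09/0.256 = 0.35 of a standard error. That benefit requires that leaving depends on scores already recorded.

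If controls are tested only before and after, the precision gain is about 1-5% at the same loss, and the bias remains. QOL-AD has no interim readings, so only the pre/post version can apply to it.

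**What to change.** 1. Reconcile the Abstract, Intervention, and Randomization and Concealment sections, and state whether controls are tested every 3 weeks.
2. **If both arms are tested:** analyse the six app outcomes with a linear mixed model on all visits. Use visit-by-group means, a parsimonious covariance such as random intercept and slope, a nursing-home (cluster) term and a small-sample degrees-of-freedom correction. Report the IG-CG difference at week 18, as change from baseline, with its 95% CI. Keep separate baseline means: Study Design has residents recruited after homes are randomised, so equal baselines cannot be presumed.
3. **If controls are tested only before and after:** do not use interim readings from one arm. Fit the mixed model, with the same cluster term and correction, to the pre and post values of both arms, so that residents with a baseline only are retained.
4. QOL-AD stays pre/post in either case.

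The cost is wording, a covariance assumption and slightly more modelling work. SPSS, the planned software, offers the model. No new data are needed under either branch.

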**Results:**

Enrollment into the study will be completed in the first half of 2022. We expect an improvement in the quality of life of people with dementia accompanied by improvements in cognitive function and physical performance. The usability of the InCoPE-App is expected to be rated well by nursing assistants.

**Conclusions:**

To date, there is no scientifically evaluated app available that enables nursing assistants without expertise in sports science to deliver an individualized exercise program among people with dementia. A highly usable and effective InCoPE-App allows nursing assistants to test cognitive function and physical performance of people with dementia and, based thereon, select and deliver an appropriate individualized exercise program based on the cognitive and physical status of an individual, even in times of a pandemic.

**Trial Registration:**

German Register of Clinical Trials DRKS00024069; https://www.drks.de/drks_web/navigate.do?navigationId=trial.HTML&TRIAL_ID=DRKS00024069

**International Registered Report Identifier (IRRID):**

DERR1-10.2196/36247

## Introduction

The COVID-19 pandemic has had drastic consequences for all areas of everyday life. In many nursing homes, routine processes had to be changed. Some activities and treatments were reduced or, in areas, canceled. Hygiene and safety measures (eg, no external exercise instructors, no group settings) and the increased workload for nursing assistants led to suspending physical exercise programs and activities, especially when delivered in a group setting. The potential consequences for nursing home residents include reduced general activity accompanied by decrease in cognitive function and physical performance and a considerable loss of an individual’s quality of life. Furthermore, these COVID-19–induced changes may also have an economic impact and may increase care expenses in the long term.

Dementia is present in up to 50% of nursing home residents [1]. The clinical symptoms of this neurodegenerative disease include, but are not restricted to, decreased cognitive skills and reduced physical performance (eg, balance and mobility) [2,3]. Many people with dementia experience a rapid progression of the disease [1]. Thus, people with dementia might be seriously affected by COVID-19–induced reduction of physical or mentally stimulating activities and similar treatments (eg, physiotherapy, ergo therapy, social interactions) in nursing homes.

In light of the absence of medication to cure dementia, physical activity is one of the major nonpharmacological interventions that has become very important in treating people with dementia. Previous reviews have mainly reported positive effects of physical activity on cognitive but also physical outcomes in people with dementia [4-8]. However, conclusive evidence is still lacking, mainly due to limited numbers of high-quality studies and large heterogeneity in methods and exercise program parameters (eg, scope, duration, intensity, contents, settings). Of note, an individual’s prior exercise experiences and preferences may also contribute to the success of an intervention. These factors, combined with the older age of people with dementia as well as the different stages and degrees of impairment, result in the highly heterogeneous samples often found in research studies. To elicit the potential effects of physical activity interventions in people with dementia, we have previously argued that individualization of the exercise program may thus be crucial [9]. To the best of our knowledge, individualized exercise programs are not sufficiently included in routines of nursing homes, and optimal or successful ways of distribution have not been reported in prior research studies.

Fundamental changes in health practice are driven by recent developments in interactive health technologies that promote health and manage illness [10]. These technologies have been reported to elicit beneficial health outcomes in various settings (eg, physical activity coaching app for breast cancer [11], Partners in School Asthma Management for inner-city elementary school children [12]). The number of digital health apps has increased exponentially, whereas the number of publications addressing their usability evaluation has remained at a low level [13]. There is still a lack of reports on the development and usability processes during app development in digital health settings. More than 95% of apps available today have not been scientifically tested, and the limited number of controlled trials of mobile technology interventions reported only modest effects [14]. However, usability is a crucial component of good practice in the development of digital apps [15]. End users’ needs are particularly important in digital health applications to ensure that individuals affected by any health issue can use the intervention appropriately, which may in turn lead to greater acceptance and thus efficiency of the intervention [16]. The ISO standard 9241-11 defines usability as the extent to which a product can be used to achieve the specified goals with effectiveness, efficiency, and satisfaction [17]. Another standard on software quality, ISO 25010, includes attributes for usability such as understandability, learnability, operability, and attractiveness [18].

Our team will develop a tablet-based mobile app aimed at supporting nursing assistants to (1) test the cognitive function and physical performance of people with dementia and (2) subsequently train people with dementia. The training is a multidomain, individualized exercise program that will be adjusted to the individual’s current physical and cognitive performance with the focus of improving physical and cognitive performance in the short and long term. In times of COVID-19, this is a novel and innovative approach that allows nursing homes to maintain a physical activity routine while complying with hygiene and safety measures, as no external exercise instructor is needed. The individualization approach used in this study in combination with the direct applicability in the setting of nursing homes is promising in terms of the individual benefit of the exercise program on physical and cognitive performance as well as quality of life. The aim of the present study is to evaluate the usability and effectiveness of the individualized exercise program provided by the Individualized Cognitive and Physical Exercise (InCoPE)-App.

